### Statistical analysis

IBM SPSS Statistics for Windows software (Version 23.0, Armonk, NY: IBM Corp.) will be used for all statistical data analyses. Descriptive statistics (frequencies, means and standard deviations, etc.) will be used to describe all data. Spearman’s correlation coefficients will be used to describe association between data. Statistical significance is defined as *P* < 0.05.

The following are the planned statistical analyses *per aim*:
*Primary aim:*
Generalized estimating equations (GEEs) will be conducted to assess the outcomes over time: 3, 6, and 12 months.

*Secondary aim:*
Linear regression analyses will be performed to assess factors predictive of Achilles tendon function. First, univariate analysis will be performed as a hypothesis-generating analysis model with ATRS-NL score (0–100) as dependent variable and a predicting factor as independent factor. Factors showing a relation with the outcome measure with a *p*-value < 0.20 will be included in a multiple linear regression analysis. Additionally, binary logistic regression will be used to determine the factors associated with returning to the pre-injury sport or recreational activity. Return to the pre-injury activity (yes or no) is the outcome variable.The Incremental Cost-effectiveness Ratio (ICER) (=Δ Cost of treatment/Δ Effect of treatment) associated with each unique treatment modality will be calculated. The ICER is calculated by taking the difference in costs associated with each possible treatment modality and its alternative (e.g. physiotherapy vs. no physiotherapy) and dividing by the difference in effect. Costs are calculated by adding the direct (e.g. cost of treatment from iMCQ questionnaire) and indirect (e.g. loss of work, from iPCQ questionnaire) costs associated with each possible treatment. Effect consists of the EQ-5D-5 L and/or ATRS-NL outcomes. The cost-effectiveness of ATR management options will herewith be determined at 3, 6, and 12 months post injury.

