### Sample size calculation

A formal sample size calculation is difficult due to the exploratory design of this cohort study as well as the lack of comparable data on ATR recovery. All eligible patients within the designated inclusion period who consent to participate will be included. Based on hospital data indicating the treatment of approximately 15 ATRs per hospital per year as well as similar studies by the research group showing a dropout of 10–20%, we estimate 50 patients will be included. This number will allow us to include at least 5 independent variables in the regression analyses based on “the rule of thumb” of 10 subjects per variable (one in ten rule) [36–38]. Other studies assessing ATR recovery usually included lower patient numbers [20, 27, 39, 40].

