#### Demographic and lifestyle data

A baseline questionnaire concerning personal subject data was constructed for specific use in this study. The items in this questionnaire concern biographical information (age), anthropometrics (height, weight), lifestyle factors (smoking, (level of) physical activity, work, urban/rural inhabitant), personal and family medical history including injuries and tendon complaints, injury (etiology, extent, and symptoms) and management factors during rehabilitation (physiotherapy).

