#### Medical data

The patients’ medical files will be inspected at baseline for medical history, medication, injury (etiology and extent (gap-size)) and ATR management (treatment delay, surgical or non-surgical treatment and methods, methods and length of rehabilitation, imaging applied) data. Additionally, the medical status will be monitored throughout the study period for information on injury, treatment and complications if applicable.

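### The p < 0.20 entry rule for the multiple regression has no cap tied to the 5 variables that the sample size section derives from 50 patients, and the survivors are then tested at 0.05 on the same data

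*Protocol article*

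**What the plan says.** The Sample size calculation section gives no formal calculation. It says "we estimate 50 patients will be included", from "approximately 15 ATRs per hospital per year" and "a dropout of 10–20" percent, and supports the number with the one-in-ten rule: "This number will allow us to include at least 5 independent variables in the regression analyses".

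The Statistical analysis section, under the secondary aim, regresses ATRS-NL on one factor at a time and calls that step hypothesis-generating. Then: "Factors showing a relation with the outcome measure with a *p*-value < 0.20 will be included in a multiple linear regression analysis". Significance is set at P < 0.05 for all analyses. The section does not tie the number of entering factors to the 5 variables.

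The factors to be screened are not listed. The Demographic and lifestyle data section collects, besides age, height and weight, "lifestyle factors (smoking, (level of) physical activity, work, urban/rural inhabitant), personal and family medical history including injuries and tendon complaints", and also injury and physiotherapy items. The Medical data section adds medication, treatment delay, type and method of treatment, and "methods and length of rehabilitation, imaging applied". The Background section names six factors with a possible influence on recovery: BMI, comorbidities, athletic status, delay in presentation, injury etiology and gap size.

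**The concern.** The two sections do not bind each other. One justifies the cohort by the number of variables a regression on 50 patients can carry. The other lets the data decide how many variables enter.

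The one-in-ten rule guards against overfitting, and overfitting arises from every factor examined, not only from those that survive a screen. Selecting factors for their association with the outcome, and then testing them at 0.05 in the same patients, gives p-values that are too small and an R-squared that is too large.

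At stake is the list of factors reported as predictive of tendon function, which the Discussion section offers to clinicians for shared decisions and individualised management.

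**Working it through.** **The plan's own figure.** 50 patients / 10 per variable = 5, so the stated number reproduces. It is the most the rule allows, whereas the text words it as a minimum. The inclusion period is not given (3 hospitals × 15 = 45 ruptures a year), so it cannot be settled whether the 50 are counted before or after dropout. If before, 50 × 0.90 = 45 or 50 × 0.80 = 40 complete, which supports 4 whole variables.

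**Candidates that could be screened.** The baseline questionnaire gives about 13: age, height, weight, smoking, physical activity, work, urban/rural, personal history, family history, etiology, extent, symptoms, physiotherapy. The medical file adds about 7: medication, treatment delay, surgical or non-surgical, treatment method, rehabilitation method, rehabilitation length, imaging. The total is about 20, before the questionnaires, physical tests and ultrasound measures of Table 1. Screening all of them is an assumption. It would leave 50/20 = 2.5 patients per candidate, or 40/20 = 2.0.

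**Screening step, by formula.** With k independent factors unrelated to outcome, the number passing is Binomial(k, 0.20), with mean 0.20k. For k = 20 the mean is 4, P(more than 5 pass) = 0.20, and P(at least one passes) = 1 − 0.80^20 = 0.988.

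**Full two-step procedure, by simulation.** Normal data were generated, factors screened at two-sided p < 0.20, and all survivors entered in least squares and tested at 0.05 (10,000 runs per scenario in the main set). Results for n = 50:

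| Candidates | More than 5 enter | At least one null factor at p < 0.05 |
|---|---|---|
| 5, independent, all null | cannot occur | 22% |
| 6, independent, all null | below 0.01% (0.2^6) | 25% |
| 10, independent, all null | 0.6% | 36–37% |
| 20, independent, all null | 20% | 56% |
| 25, independent, all null | 38% | 62% |
| 30, independent, all null | 57% | 67% |
| 20, all null, all pairs correlated 0.2 | 21% | 45–46% |
| 20, all null, all pairs correlated 0.3 | 23% | 37% |
| 20, all null, all pairs correlated 0.5 | 24% | 18% |
| 20, all null, blocks of four correlated 0.3 | 21% | 48% |
| 20, all null, blocks of four correlated 0.5 | 24% | 34% |
| 20, of which 3 true (r = 0.35) | 62% | 42–44% |

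For 20 independent null candidates the mean apparent R-squared is about 0.22, where the truth is 0. With n = 40 the false-factor rate is 54–55%, so it hardly depends on sample size. The sample size matters for the patients-per-variable argument.

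**Comparison.** Five tests at 0.05 without any screen give 1 − 0.95^5 = 0.226, close to the simulated 22% for 5 candidates.

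**The case against.** The strongest reply is that the article never says 20 factors will be screened. The two data sections list what is collected, and the only factors tied to recovery are the six in the Background section. With those six, more than 5 would almost never pass by chance and the false-factor rate is about 25%. A candidate list may also stand in the full protocol or analysis plan. This stands: the missing list is not itself a finding, and the percentages are conditional. It does not answer the stated entry rule, which has no cap whatever the list.

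A second reply is that the design is exploratory, the aim is secondary and the screen is labelled hypothesis-generating. This lowers the severity. But the label is attached to the univariate step only. The multiple regression is meant to assess predictive factors, under a stated significance level.

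A third is that the sample size section only remarks on capacity. That is fair, and even with 20 independent null candidates about 80% of studies would stay within 5. With three true predictors among them, most would not.

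A reader might infer three stronger claims that the document does not support:

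- That more than half of such studies yield a chance predictor. This needs about 20 or more candidates, independent and all unrelated to outcome. Modest correlation, or a few true predictors, brings 20 candidates below one half.
- That length of rehabilitation is a planned predictor, and so a case of reverse causation. It is listed only as medical-file data.
- That the screen discards confounders. The stated purpose is prediction, so this objection does not apply directly.

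**Conclusion.** The concern holds in this form: the plan states an uncapped p < 0.20 entry rule, unconnected to the 5 variables (4 if 40 complete) used to justify 50 patients, and tests the survivors at 0.05 on the same data.

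The size depends on a candidate number that the article does not give. For 10 to 30 candidates with the correlations tried, the chance of at least one false significant factor is roughly 20 to 65% (computed extremes 18% and 67%), against about 22% for 5 candidates. These figures assume normal data and two-sided tests.

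It does not follow that the findings would be mostly noise. What follows is that the final p-values and R-squared would lack their nominal meaning. This should be fixed, but given the exploratory secondary aim it is not a condition for the study to proceed.

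**What to change.** In the Statistical analysis section, replace the p < 0.20 entry rule by one of the following:

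- A list of at most 5 predictors (4 if about 40 are expected to complete), named before analysis, all known by the month-3 visit, entered together and reported with 95% confidence intervals. The six factors in the Background section are a natural source; primary treatment is not among them. Other factors are shown descriptively.
- If a wider search is wanted, one penalised model on a declared candidate list, with bootstrap correction for optimism.

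In the Sample size calculation section, count the one-in-ten rule on candidates rather than on survivors, and word the 5 as a maximum.

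Only analysis wording changes; no patients, visits or data are added. The cost is that fewer factors get an adjusted estimate. Five tests at 0.05 still carry about a 22% chance of a false finding, so intervals should lead the report.

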## Discussion

There is an increasing incidence of ATR, and numerous long term impairments are reported. Despite several randomized controlled trials comparing various methods of primary treatment, clinical treatment and rehabilitation guidelines are still lacking. This multicenter prospective cohort study focuses specifically on the rehabilitation phase. This study will contribute to the primary treatment and rehabilitation of ATRs by providing insight into (1) ATR recovery, (2) novel imaging for monitoring recovery, (3) (barriers to) RTS and (4) cost-effectiveness of management. These data will provide a broad understanding of ATR recovery as well as provide data on novel imaging and costs, thereby providing knowledge for clinicians in shared decision making and individualizing ATR management.

## Abbreviations

AAOS: American Academy of Orthopedic Surgeons
ACL: Anterior Cruciate Ligament
ATR: Achilles tendon rupture
ATRS: Achilles Tendon Total Rupture Score
GEE: Generalized estimating equation
ICER: Incremental Cost-effectiveness Ratio
iMCQ: Medical Consumption Questionnaire
iMTA: Institute for Medical Technology Assessment
iPCQ: Productivity Cost Questionnaire
I-PRRS: Injury psychological readiness return to sport scale
MCL: Medical Center Leeuwarden
MHG: Martini Hospital Groningen
OSTRC: Oslo Sport Trauma Research Center
PROMs: Patient-reported outcome measures
ROM: Range of motion
RTS: Return to sport
TSK: Tampa Scale of Kinesiophobia
UMCG: University Medical Center Groningen
UTC: Ultrasound Tissue Characterization
